	**Measure moment**			
**Measures**	**T**_ **0** _	** *T* **_ ** *1m* ** _	** *T* **_ ** *4m* ** _	** *T* **_ ** *10m* ** _
** *Anthropometrics* **				
(Weight, height, waist and hip circumference, skinfolds)	x		x	x
** *Questionnaires* **				
Time spent active and non-active gaming	x	x	x	x
Physical activity and sedentary screen time	x	x	x	x
Consumption of snacks and sugar sweetened beverages	x	x	x	x
Companions for active/non-active gaming				x
Game consoles and applications owned	x	x	x	x
** *Process evaluation (only in intervention group)* **				
**1) Adherence to the intervention**				
Usage of Move games		x	x	x
Reasons for not playing (the minimal of one hour per week)		x	x	x
**2) Opinion of the Move games and the intervention**				
Enjoyment with respect to playing the Move games		x	x	x
Most played Move game		x	x	x
Most enjoying Move game		x	x	x
Ease of use		x	x	x
Perceived competence		x	x	x
Perceived physical exertion of playing Move games				x
Opinion on the amount of provided Move games				x
Self purchased Move game				x
**3) Game context**				
Move game companions				x
Location of PlayStation Move console				x
**4) Potential adverse effects** (occurrence of injuries because of playing with the Move games)				x
**5) Activity replacement**			x	x
**6) Intention to continue playing the Move games**				x

*T*_
*0*
_, Baseline measurement; *T*_
*1m*
_, Measurement one month after baseline; *T*_
*4m*
_, Measurement four months after baseline; *T*_
*10m*
_, Measurement ten months after baseline.

The study was approved by the Medical Ethics Committee of the VU Medical Centre.

### Blinding

It is not possible to perform the randomization blind, because based on the randomization the adolescents receive an active game upgrade package or not. At T_0_ the measures are conducted blind for participants and research assistants regarding group assignment. At the end of the T_0_ measure the randomization takes place and therefore the measures at T_4m_ and T_10m_ cannot be conducted blind for participants or assessors. The intervention group receives new games at T_4m_ and the control group receives their Move package at T_10m_. Data analyses are not conducted blind.

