## Methods/Design

### Design

The efficacy of the active game intervention is evaluated in a randomized controlled trial among adolescents aged 12 to 16 years old and their families. Families are randomly assigned to the intervention or control group after baseline assessment by the researcher or research assistant using a pre-determined randomization list. The randomization list consists of a row with the numbers one and two in a random order and is based on a block randomization scheme, with blocks of 100, obtained from an online computer program (http://www.randomization.com). Participants are assigned to one of the research groups based on this randomization list in order of checking out after they finish the baseline measures. The intervention group is exposed to the active game intervention and the control group is asked to continue their normal game play behavior and they receive the material belonging to the intervention at the end of the study. Measures are taken at baseline (T_0_) (adolescent anthropometrics and questionnaire), after one month (T_1m_) adolescent questionnaire (including process evaluation for intervention group adolescents), four months (T_4m_) adolescent anthropometrics and questionnaire (including process evaluation for intervention group adolescents); and ten months (T_10m_) adolescent anthropometrics and questionnaire (including process evaluation for intervention group adolescents) (Table 1). Primary outcomes are adolescents’ measured BMI-SDS (SDS = adjusted for mean standard deviation score), waist circumference-SDS, hip circumference and skinfolds thickness. Secondary outcomes are adolescents’ self-reported sedentary behavior, and consumption of sugar-sweetened beverages and snacks. Additionally, physical activity behavior excluding active game play is assessed to check whether the active game intervention was at the expense of physical activity.

**Table 1 T1:** Design scheme

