The present study is subject to some limitations that need to be acknowledged. Although we obtain the primary outcome measures objectively (e.g. adolescents’ height, weight, waist/hip circumference and skinfolds), the secondary outcome measures (e.g. adolescents’ physical activity, sedentary behavior, consumption of snacks and sugar-sweetened beverages) are self-reported and thus liable to social desirability and recall bias. However, this will occur in both groups resulting in potential bias towards the null.

In conclusion, this trial will provide important new information on the potential contribution of active games to the prevention of excessive weight gain in adolescents and the process evaluation will provide relevant information for future active games studies on factors hindering or promoting active game play.

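### The reason given for unmasked follow-up assessors does not hold, so three tape- or calliper-based primary outcomes carry reducible detection bias

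*Protocol article*

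**What the plan says.** The Blinding section of the protocol article makes four statements.

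- On allocation: "It is not possible to perform the randomization blind, because based on the randomization the adolescents receive an active game upgrade package or not".
- On baseline: "At T_0_ the measures are conducted blind for participants and research assistants regarding group assignment".
- On follow-up: "the measures at T_4m_ and T_10m_ cannot be conducted blind for participants or assessors". The article derives this from the fact that families are randomised once baseline is finished. No other reason is given.
- On analysis: "Data analyses are not conducted blind".

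The same section adds that the intervention group gets new games at T4m and the control group its package at T10m.

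The Design section names four primary outcomes: BMI-SDS, waist circumference-SDS, hip circumference and skinfold thickness. It has families assigned "by the researcher or research assistant using a pre-determined randomization list", in the order in which they check out after baseline.

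The Measurements section has trained assistants measure on days fixed in advance at central venues, with home measurement for those who cannot attend. Each measurement is taken twice. A third reading is required if the two differ by more than a fixed limit, and the outlier of the three is then dropped.

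The limitations paragraph of the Discussion says "we obtain the primary outcome measures objectively" and confines its remarks on bias to the self-reported outcomes. It does not mention unmasked assessors.

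**The concern.** The plan treats two different things as one. Adolescents in this trial cannot be masked, because they know whether they have the games. The person holding the tape or calliper does not have the games and need not know who does. Treating assessor masking as impossible rules out a safeguard that the visit format could support.

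Tape position and tension, and the siting and timing of a calliper reading, all leave room for the operator's expectation. If assessors know the group and hope for smaller values under the intervention, readings can drift differently in the two arms. That moves the estimated effect itself. A larger sample does not remove it, and neither does adjustment for baseline, because the baseline was taken blind and does not carry the shift.

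**Working it through.** **1. Does the stated reason support the conclusion?**

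| Statement | For participants | For assessors |
|---|---|---|
| Randomisation takes place at the end of T0 | They learn their group, so later masking is lost | They learn the group only if they made the allocation or are told it |
| Games or packages are given at T4m and T10m | Already unmasked | A possible cue, depending on who hands over and when; the article does not say |
| Measurement by trained assistants at central venues on fixed days | Not relevant | Allows measuring to be separated from allocation and handover |

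The conclusion follows for participants and not for assessors.

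**2. Which primary outcomes are exposed?** Waist and hip are taken by tape, and skinfolds by calliper at four sites. That is three of the four. BMI-SDS comes from an electronic scale and a stadiometer and is much less dependent on the operator. Anthropometry is taken at T0, T4m and T10m only, so the T1m questionnaire is not affected.

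**3. Would the quality rule catch a drift?** Let the true value be x, the random errors of the two readings e1 and e2, and the assessor's systematic shift b.

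- Reading 1 = x + e1 + b; reading 2 = x + e2 + b.
- Difference = e1 − e2. The shift cancels, so the limits (1 cm for waist and hip, 1 mm for skinfolds) are met or missed regardless of b.
- Mean = x + (e1 + e2)/2 + b. The shift stays in full.

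A third reading carries the same b, and dropping an outlier does not remove it. If the average shift is bI in the intervention arm and bC in the control arm, the estimated difference is biased by bI − bC. The rule controls scatter within an observer, which is its declared purpose. It says nothing about bias.

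**4. How much could it matter?** The documents give no bias, so any figure here is an assumption. Suppose an exposed outcome has 80% power at two-sided 0.05 (two-sidedness is itself assumed) for its planned effect, and suppose the bias is a fraction f of that effect. Then the standardised shift is f × (1.960 + 0.842) = 2.802f. With no true effect, the chance of a significant result is 1 − Φ(1.960 − 2.802f) + Φ(−1.960 − 2.802f). Taking the Sample size section's 0.5 kg with SD 1.5 kg as the scale (0.5/1.5 = 0.333 SD):

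| f | Bias in SD units | Actual two-sided error |
|---|---|---|
| 0 | 0 | 5.0% |
| 0.10 | 0.033 | 5.9% |
| 0.20 | 0.067 | 8.7% |
| 0.30 | 0.100 | 13.4% |
| 0.50 | 0.167 | 28.8% |

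Those planning figures are for body weight, which is little exposed. The table borrows their standardised size for the tape and calliper outcomes, for which the article gives no planned effect or SD.

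**The case against.** The strongest reply is practical. Adolescents know their group and may say so. Some are measured at home. The Intervention section requires encouragement at each contact, so group-specific talk is built into the visits. No staffing per venue is given, so separate people for measuring and handover cannot be taken for granted. All of this stands and means that masking would be partial. It does not rescue the stated reason, and partial masking still reduces bias.

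It can also be said that the Discussion's claim of objectivity only contrasts measured with self-reported outcomes. That is a fair reading, but assessor knowledge is still absent from the limitations. On analysis, models and covariates are specified in advance and the lack of blinding is disclosed, so coding the arms is a modest gain.

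Several stronger readings are tempting and are not supported.

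- *Concealed allocation is declared impossible.* A reader might infer this from "It is not possible to perform the randomization blind". The reason attached concerns the treatment received, so it reads as a statement about masking. The article never says that upcoming assignments cannot be concealed.
- *The list is open to staff.* The Design section does not say whether it is open, sealed or released line by line. Consent and baseline precede allocation. Blocks of 100 make guessing hard: with m = 50 per arm, the expected run of fully determined assignments at the end of a full block is 2m/(m + 1) = 100/51, about 2. What could remain is a change in check-out order, and only if the list is visible.
- *The handover is what unmasks assessors.* The article attributes unmasking to the timing of randomisation and does not say who hands over or when.
- *The reading limits set the size of the bias.* They do not, because a common shift of any size passes.
- *Staff choose the outlier.* The third reading is triggered by fixed limits, and no discretion is described.
- *All primary outcomes are equally at risk.* BMI-SDS is not.

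**Conclusion.** The point holds in this limited form. The Blinding section's reason for unmasked assessors at T4m and T10m is a non sequitur, and it leaves three of the four primary outcomes open to detection bias that could be reduced though not eliminated. The size is unknown. Under the assumptions above, a bias of one tenth of the planned effect would hardly change the error rate (5.9%), while one of half would bring it to 28.8%. The conclusion itself does not depend on that table. It rests on the wording of the Blinding section, on the operator-dependence of tape and calliper measurements, and on the cancellation of a common shift in duplicate readings.

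This should be changed, but it does not invalidate the trial. Concealment of the list is a secondary matter on which the article is silent, not shown to be at fault.

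**What to change.** 1. At T4m and T10m, have anthropometry done first by research assistants who did not allocate that family and are not told its group.
2. Give packages, encouragement and any other group-specific contact afterwards, at a separate check-out. Ask families beforehand not to disclose their group.
3. Record for each visit whether the assessor stayed masked, including home visits and disclosures.
4. Code the arms A and B until the models for the main comparison are final. Keep the process evaluation data, which exist for the intervention arm only, out of that file. The per-protocol analysis will necessarily reveal the arms and should come later.
5. Rewrite the Blinding section so that it gives the true reason for whatever assessor masking is not done, and list the remaining unmasked assessment as a limitation in the Discussion.
6. State how the randomisation list is kept. Sealed envelopes or central release would remove any scope to alter check-out order.

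The cost is mainly a changed order of tasks at the visits and some extra logistics where few staff are present. If the follow-up visits are already over, items 4 and 5 can still be done, together with a statement for item 6 of how the list was kept.

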### Participants

The current study focuses on adolescents aged 12–16, who are the main participants of the study. Additionally the family members of the adolescent (parents and siblings aged 8–18 years old) are included in the study but they are not used for current analyses. Inclusion criteria are:

•Adolescent plays ≥ 2 hours of non-active video games per week

•Adolescent does not play active games yet, or less than once a week.

•Adolescent is physically and mentally able to play active games

•Adolescent has access to a PlayStation3 in his or her home.

•Family does not have a Move upgrade for PlayStation3

•Adolescent lives in the participating household (assuring sufficient access to the Move games provided as part of the intervention) at least 4 days a week.

•At least one family member (parent or sibling aged 8–18 years old) is willing to participate in the study (filling in questionnaires).

### Sample size

Sample size calculation is performed to estimate how many adolescents should be included to detect a significant difference of 0.5 kg excess body weight between the intervention and control condition during the follow-up measurements (primary analysis). The 0.5 kg excessive weight gain is based on calculations in adults, because calculations for adolescents were lacking at that time. Adult individuals may gain on average 0.5 kg excess body weight per year, which results from an energy imbalance of only 70 Kcal per week per year [43]. We computed, based on energy expenditure studies, that an excess weight gain of 0.5 kg, may be prevented by substituting one hour per week of non-active gaming by playing active games [45]. To have sufficient power to detect a clinically relevant difference in excess weight gain of 0.5 kg (SD = 1.5 kg) between the intervention and control condition during follow up, with a power of 0.80, alpha .05 and an intraclass correlation coefficient (ICC) for within-subject clustering of observations of 0.7, 99 participants in each condition are needed. Taking into account an anticipated drop-out of 20%, a total of 119 adolescents per condition needs to be recruited.

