### Intervention

Adolescents assigned to the intervention group receive a PlayStation®Move upgrade package to play active games on a PlayStation3 console. PlayStation®Move uses a handheld motion controller wand and a motion-capture PlayStation®Eye camera that tracks the position, and inertial sensors in the wand to detect its motion. In this way every movement of the player is mimicked on-screen in the game. Although, there are multiple active game systems (such as Nintendo Wii, Dance Dance Revolution, Microsoft Xbox Kinect, PlayStation2®EyeToy) available on the market, the PlayStation®Move was chosen for the current study for several reasons. First, a survey study showed that the PlayStation was the most frequently owned game console among 12–16 year old adolescents [19]. So by choosing an application that is compatible with the PlayStation, we optimize the chances for recruiting sufficient participants. Second, the active game system for the PlayStation is one of the newest on the market at time of the study, making use of the most sophisticated technology, and may be more affordable (around €50) than other consoles or active game upgrades (e.g. Microsoft Kinect (around €135)).

As mentioned in the introduction previous studies showed that attention should be paid to (ongoing) participation in active game play, therefore we include several motivation enhancing intervention elements. Since variation in games is important [22,46,47], families receive four active Move games (Sport Champions, Move Fitness, Start the Party and Medieval Moves) at the start of the study and two more (Dance Star Party and Sorcery) after four months. Social and family play is important [22,44], and we provide two controllers to promote playing together with family and friends. Further, research has shown that providing instruction to use the active games seems an important addition to providing the games for physical activity promotion [46,48], therefore we explicitly encourage participants at each contact moment to substitute non-active gaming with active gaming as much as possible but at least one hour per week. One hour per week corresponds with approximately 70 kcal (representing the energy imbalance that can result in excessive weight gain) [43], and was regarded as a feasible change.

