The encouragement for the intervention group to replace at least one hour per week of non-active gaming with active gaming, is based on calculations in adults demonstrating that excessive weight gain can be prevented if the energy balance is affected by 70 kcal per week. This was the best estimation that could be made when designing the study, because no child specific equation was available at that time. Recently, Hall et al. [61] developed and validated a model that quantifies the energy imbalance underlying excess bodyweight in children and calculates the necessary intervention magnitude to achieve bodyweight change in children. This model shows that around 116 extra kcal per week should be expended to prevent an excessive weight gain of 0.5 kg in children with an average age of 14 years old. As studies have shown that active gaming can elicit an energy expenditure of 381 kcal [23], one hour of active gaming (assuming it does not replace more vigorous activities such as sports) should in theory be sufficient to prevent excess weight gain in children.

A concern regarding promoting active game play is that active game play might replace traditional forms of physical activity (e.g. cycling, playing outside) because these activities elicit greater energy expenditure and may therefore contribute more to prevention of excessive weight gain than active gaming. In a descriptive Dutch study among active gaming adolescents and their parents, adolescents reported that they thought active gaming had replaced sedentary activities [45]. However, this was asked in retrospect after adolescents were already playing active games, and recall bias might have occurred. To get more insight in whether stimulating active gaming will lead to replacement of sedentary activities or whether it takes adolescents away from physical activities in which they already participate, the current study also evaluates the effect of providing active games on sedentary behavior and physical activity.

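### The sample size rests on 0.5 kg of body weight, which is not a listed primary outcome, and carries an adult per-year figure unchanged to follow-up at 4 and 10 months

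*Protocol article*

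**What the plan says.** The Sample size section sets the target as "0.5 kg excess body weight between the intervention and control condition during the follow-up measurements (primary analysis". It continues "To have sufficient power to detect a clinically relevant difference in excess weight gain of 0.5 kg (SD = 1.5 kg", takes power 0.80, alpha .05 and a within-subject ICC of 0.7, and obtains 99 per condition, raised to 119 for 20% drop-out. The source of the 0.5 kg is given as "Adult individuals may gain on average 0.5 kg excess body weight per year". The section says openly that this is an adult figure, used because none existed for adolescents.

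The Design section names the primary outcomes as BMI-SDS, "waist circumference-SDS, hip circumference and skinfolds thickness". The Abstract and the first hypothesis in the Background give the same four. In the Measurements section, weight is recorded and enters BMI, but it is not an outcome in its own right. Table 1 places anthropometry at baseline, 4 months and 10 months, and the first hypothesis compares the groups at those two follow-up visits.

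The Abstract and the Discussion describe the trial as adequately or well powered.

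**The concern.** Two mismatches lie in the same calculation.

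- **Outcome.** The comparison that is powered, and labelled primary, concerns a variable that the outcome list does not contain. The article gives no target difference and no SD for any of the four listed outcomes.
- **Time base.** A one-year amount is used as the difference to be seen at visits that end at 10 months. The adult origin is disclosed. The difference between a year and 4 or 10 months is not mentioned.

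What is at stake is how a null result would be read. If BMI-SDS, waist-SDS, hip circumference and skinfolds all show no difference, the claim of adequate power invites the conclusion that no relevant effect exists. The sample-size section does not license that conclusion for any of them.

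**Working it through.** **Inputs from the Sample size section.** Difference 0.5 kg, SD 1.5 kg, power 0.80, alpha 0.05, ICC 0.7, 99 per condition. Sidedness is not stated; two-sided is assumed.

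**Step 1: the plan's own figure.** For one measurement per person, n per arm = 2 × [1.5 × (1.96 + 0.84) / 0.5]² = 141.28 (unrounded normal quantiles), so 142. Repeated follow-ups multiply this by a variance factor f:

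- f = (1 + 0.7)/2 = 0.85, the usual factor for the mean of two follow-ups: 120.1, so 121.
- f = 0.7, the ICC itself: 141.28 × 0.7 = 98.9, so 99.

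Of the standard variants tried, only f = 0.7 returns the stated 99. Both factors are carried forward so that the effect of the time base can be seen apart from the choice of f.

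**Step 2: the 0.5 kg on the trial's time scale.** Assumptions: linear accrual over the year, substitution at the encouraged minimum of one hour per week, no change in energy intake, and SD constant at 1.5 kg.

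- 4 months: 0.5 × 4/12 = 0.167 kg
- 10 months: 0.5 × 10/12 = 0.417 kg
- Mean of the two visits: (0.167 + 0.417)/2 = 0.292 kg

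**Step 3: power at 99 per condition.** Power = Φ(δ / [1.5 × √(2f/99)] − 1.96).

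| Difference | f = 0.7 | f = 0.85 |
|---|---|---|
| 0.5 kg (as planned) | 80% | 72% |
| 0.417 kg | 65% | 56% |
| 0.292 kg | 37% | 32% |

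Worked example, f = 0.7 and 0.417 kg: the standard error is 1.5 × √(1.4/99) = 0.178; 0.417/0.178 = 2.34; Φ(2.34 − 1.96) = 65%.

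In the f = 0.85 column the full 0.5 kg already has only 72%. The time base accounts for the fall from 72% to 56% or 32%, not for the whole distance from 80%.

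For 80% power, n per arm would be 143 (f = 0.7) or 173 (f = 0.85) at 0.417 kg, and 291 or 353 at 0.292 kg.

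**Step 4: sensitivity to the meaning of the SD.** The sentence attaches 1.5 kg to the weight gain, and steps 1 to 3 read it so. Suppose instead that it is the SD of a follow-up value with baseline correlation 0.7, analysed with the planned baseline adjustment over two follow-ups. Then f = 0.85 − 0.7² = 0.36. Power at 99 per condition becomes about 90% for 0.417 kg and 63% for 0.292 kg. Under that reading the original 0.5 kg would need only 141.28 × 0.36 = 50.9, so 51 per arm. The stated 99 therefore suggests that the plan did not use it.

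**Step 5: the four primary outcomes.** With no difference and no SD given for them, power cannot be computed in either direction. Turning 0.5 kg into BMI-SDS would need heights, the reference distribution and a residual SD, none of which the article supplies.

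**The case against.** The strongest reply has four parts.

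- **The article is condensed and its power claim is general.** It does not assert 80% power outcome by outcome, and an SD source may sit in a fuller document. That is fair. But the article does state a basis for its sample size and calls it the primary analysis, and that basis disagrees with its own outcome list. This is a contradiction in the text, not an omission.
- **One hour is a floor.** The Intervention section encourages as much substitution as possible, and the Background proposes lower intake as a second route. On the linear scaling, 0.5 kg at 10 months needs 70 × 12/10 = 84 kcal per week, or 1.2 hours at 70 kcal per hour. On the child figure, treated as per-year, it needs 116 × 12/10 = 139 kcal, about 2 hours. Entry requires at least 2 hours per week of non-active gaming. A reader might infer that 0.5 kg is out of reach within follow-up; the documents do not support that. The powers in step 3 hold only under the stated assumptions.
- **The child model does not undermine the target.** A reader might infer that "This model shows that around 116 extra kcal per week should be expended to prevent an excessive weight gain of 0.5 kg in children" contradicts the 0.5 kg. It does not: it concerns the same 0.5 kg and changes only the weekly energy needed. The Discussion raises it openly and says that the adult figure was the best available at design.
- **The energy figures are answered in the text.** The Discussion argues that one hour suffices because "active gaming can elicit an energy expenditure of 381 kcal". A smaller tension remains, since the Intervention section says "One hour per week corresponds with approximately 70 kcal". Seventy is below 116 and 381 is above it (381/70 = 5.4). A reader might take 381 as gross expenditure, but the article does not say whether it is gross or net of the gaming replaced.

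**Conclusion.** The point stands on both mismatches. Weight in kg is powered as the primary analysis but is not a primary outcome, so neither the 80% nor the claim of adequate power is supported for BMI-SDS, waist-SDS, hip circumference or skinfolds. This part needs no assumption.

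The per-year figure is applied unchanged to 4 and 10 months. Its size depends on the step 2 assumptions and on the variance factor: about 56% to 65% power for the 10-month difference and 32% to 37% for the average of the two visits, if 1.5 kg is the SD of gain. If it is the SD of a follow-up value, the 10-month figure is about 90%. That alternative would ease the time-base problem but would leave the outcome mismatch untouched.

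A reader might go further and conclude that the trial is underpowered for its primary outcomes. The documents do not show that; they show that its power for those outcomes is unknown. The 70 and 381 kcal figures are a minor matter of reconciliation.

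**What to change.** 1. Restate the calculation as the BMI-SDS difference detectable with 80% power at the planned analysed number, giving the SD, what it is the SD of, and its source. The stated number is 99 per condition; 119 less 20% is 95.
2. If the weight rationale is kept, give the expected effect at 4 and at 10 months rather than per year, state the accrual assumption, and say whether 1.5 kg is the SD of gain or of a follow-up value.
3. Limit the power claim in the Abstract and Discussion to what the recalculation shows.
4. Minor: reconcile the roughly 70 kcal per hour in the Intervention section with the 381 kcal in the Discussion, saying for each whether it is net of the gaming replaced.

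The cost is one recalculation and some rewording, and a stated power that will probably look less favourable. Intervention, recruitment and measurements are unaffected.
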